#### Study population main study

The PCPs provided the names and addresses of all their listed patients of 75 years or older and living at home. All persons received a health survey including the COOP-WONCA charts in order to identify the 20–25% elderly with the frailest functional health. The cut-offs per chart were based on a combination of reference data and our pilot data [22]. Inclusion and exclusion criteria are summarized in Table 1.

**Table 1 T1:** Inclusion and exclusion criteria

Inclusion:	• Age 75 years and over and listed as general practice patient
	• Living at home
	• Frail: Self reported Health score in the worst quartile of at least two of six COOP-WONCA charts (scoring range: 1, excellent, to 5 very bad): Overall health ≥4; Physical fitness ≥5; Changes in health ≥4; Daily activities ≥4; Mental health ≥3; Social activities ≥3
Exclusion:	• Terminally ill as determined by PCPs
	• Persons with dementia symptoms according to MMSE or 7-minute screen
	• Living in residential homes.
	• Participating in other research projects

#### Intervention(s)

The scores of all persons who filled out the health survey and positively responded to the care offer were analyzed. The intervention consisted of 7 elements; (1) All frail persons and randomized to the intervention were contacted by one of eight trained nurses. In the first visit the nurses assess the health status and care needs by the Resident Assessment Inventory Home Care version (RAI-HC), a structured and computerized multidimensional geriatric instrument that enables direct and validated identification of problem areas [23,24]. The RAI-HC holds about 120 items and 30 domains of health and service needs (Table 5). It takes between 45 to 60 minutes to complete; (2) In our intervention the list of problems is discussed with the patient to determine whether additional care is needed.

**Table 5 T5:** Case example of assessment by a nurse with the RAI-HC: triggered health risks

*Client Assessed Problem*	*Observed*	*Action undertaken earlier?*	*Relevant action now?*	*Immediate action?*	*Action later?*
1. ADL / Revalidation potential	X		X		
2. IADL / more formal care					
3. Health promotion					
4. Risk intramural admission					
5. Communication impairment					
6. Visual impairment					
7. Alcohol abuse					
8. Cognition					
9. Behavior					
10. Depression and Anxiety					
11. Abuse					
12. Social functioning					
13. Heart and lungs	X		X		
14. Dehydration	X			X	
15. Falls					
16. Nutrition					
17. Dental health					
18. Pain					
19. Bedsores	X	X			
20. Skin and food problems	X		X		
21. Compliance					
22. Vulnerable support system					X
23. Medication management					
24. Palliative care					
25. Preventive health	X				X
26. Psychofarmaca use	X	X			
27. Reduced service package					
28. Environment					
29. Feces incontinence					
30. Urinal incontinence catheter	X				

Therefore the nurse and the patient make a hierarchy of the problems; (3) The nurses design and execute individual suited care-plans that comply with patient priorities; (4) The nurses are case-managers and offer to visit the patients at least 5 times in a year in order to execute and monitor the care-plan, to evaluate whether the care-needs have changed and adapt the care/plan when needed; (5) The nurses also meet the PCPs on a regular basis to discus the care plans and to assure that medical actions are carried out by the PCPs; (6) To assure the quality of care, the nurses receive regularly educational updates and organize monthly meetings to discuss problematic cases. Two staff members supervise them. A national Dutch guideline on home care nursing of frail elderly patients was available [25]. This guideline was used to protocolize nurse interventions whenever possible; (7) The care plan is left at the patients' house to enable other visiting health professionals to take notice of and report on the care plan.

#### Outcomes and measurements

Table 4 provides an overview of all outcomes and measurements in the study.

**Table 4 T4:** Measurement scheme

*Health screener*	*Instrument*	*T-1*	*T0*	*T1*	*T2*
				*6 months*	*18 months*
Functional Health status	COOP-WONCA	X		X	X
ADL & IADL	GARS	X		X	X
Cognitive decline	IQCODE self report	X			
Depressive symptoms	CES-D	X		X	X
Chronic diseases	Chronic diseases list	X			X
Mobility and Falls	Questionnaire	X		X	X
Body Mass Index	Questionnaire	X			
Weight change	Questionnaire	X			
Demographics	Questionnaire	X			
Behavioral problems	Questionnaire	X			
Incontinence	Questionnaire	X		X	X

*Main Outcomes*					
a. Health related Quality of life	SF36 + EQ5D		X	X	X
b. Hospital admissions	Patient + hospital database		X	X	X
c. (Days until) Institutionalization	PCP + nursing homes				X
d. (Days until) Mortality	Relatives + PCP				X
e. Health resource utilization	Self report + PCP + hospital + pharmacy databases		X	X	X

PCP = Primary Care Physician

GARS = Groningen Activity Restriction Scale

CES-D = Center for Epidemiological Studies – Depression Scale

IQCODE = Informant Questionnaire on Cognitive Decline in the Elderly

SF36 = Short Form 36 item version

EQ5D = EuroQuality of life

X = measurement

T-1 = pre randomization health screening

T0 = Measurement immediately after randomization

T1, T2 = Follow-up measurements

Outcomes are:

1. Health related quality of life as measured with the Short Form 36 (SF-36), and Quality Adjusted Life Years by health utilities based on Euroqol (EQ-5D) [26,27];

3. (Days until) institutionalization: Hospital stay, placement in nursing home or home for the elderly are surveyed and crosschecked at institutes;

4. (Days until) mortality as checked with the PCPs;

5. Direct costs as measured by patient questionnaires with three-monthly recall periods. These self-report data are supplemented by data from the centralized regional pharmacy database (medication use), regional hospital check, and nursing home checks. In case patients are not able to fill out the forms themselves a close relative will be approached (Table 4).

#### Sample size calculation

For an anticipated Health related Quality of Life benefit on at least two SF-36 domains with minimal relevant effect size Cohen's D = 0.5, 64 persons per group are required with a two sided alpha of 0.05 and 80% probability. Anticipating on an annual attrition of 20% (mortality, inability to respond, unwilling) 75 persons per group will be needed.

In a trial of 650 persons a reduction of 10% in hospital admission, institutionalization and mortality can be detected with a two-sided alpha of 0.05 and 80% probability (320 persons needed per group). Effect estimates are based on previous meta-analyses [11,12].

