### Costs

Aging is costly. About one third of the health care expenditures in industrialized countries relate to persons 70 years or older [19]. Nursing homes, homes for the elderly and hospital beds are occupied mainly by elderly. Elderly are massive consumers of medication. Elderly consume most home care. When the number and portion of (frail) elderly increases the health care costs will explode. Among community dwelling elderly with usual care the median annual nursing home and hospital admission rate is 2.4% (range 0–40%) respectively 26% (range 5–56%). Among frail elderly median annual admission rates are 15% and 45% respectively [11,12].

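### 320 per group does not give the stated 80% power for hospital admission at the article's own frail-elderly rate: about 73% if the 10% reduction is absolute, 21–33% if it is relative

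*Protocol article*

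**What the plan says.** The second paragraph of the Sample size calculation covers the event outcomes. For a trial of 650 it says that "a reduction of 10% in hospital admission, institutionalization and mortality can be detected with a two-sided alpha of 0.05 and 80% probability", with 320 needed per group. One number and one power therefore serve three outcomes. The paragraph gives no control risk and does not say whether 10% is a difference in percentage points or a proportion of the control risk. It attributes its effect estimates to two earlier meta-analyses (references 11 and 12).

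The Costs section of the Background cites the same two references for event rates, in the order nursing home, then hospital: "Among frail elderly median annual admission rates are 15% and 45% respectively". These are the only rates in the article for frail elderly people, the population enrolled. The same section gives medians for all community-dwelling elderly of 2.4% (nursing home) and 26% (hospital).

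Follow-up is 18 months (Design). Block randomization gives equal groups within practices. The dichotomous outcomes are compared by chi-square tests and logistic regression (Data-analysis). Recruitment reports 658 randomized.

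**The concern.** For a fixed absolute difference, the number needed depends strongly on the control risk. A single figure cannot give 80% power for the same 10-point fall at both 15% and 45%. For a fixed relative reduction the dependence is stronger still. So the sentence can be checked against the article's own rates, and hospital admission is the outcome most likely to fall short, because its risk lies closest to 50%.

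What is at stake is how a null result is read. Hospital admission is listed among the main outcomes in Table 4. A reader who takes the sentence at face value could conclude that a non-significant result makes a 10% reduction unlikely, with 80% power behind that conclusion. The error would be modest if 10% is absolute and large if the reader takes it as relative.

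**Working it through.** **Inputs.** Two-sided alpha 0.05, power 80%, 320 per group and a 10% reduction (Sample size calculation). Control risks of 45% a year for hospital and 15% for nursing home (Costs). Equal allocation and 18 months of follow-up (Design). 658 randomized, so 658 / 2 = 329 per group (Recruitment).

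**Formula.** For two proportions p1 and p2 with mean p:

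n per group = [1.960·√(2p(1−p)) + 0.842·√(p1(1−p1) + p2(1−p2))]² / (p1−p2)²

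Power at n = Φ{ [|p1−p2|·√n − 1.960·√(2p(1−p))] / √(p1(1−p1) + p2(1−p2)) }

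**Where the stated 320 comes out.** An absolute 10-point fall gives 316, 323 and 329 per group from control risks of 33%, 34% and 35%. The exact solution is about 34%, with a mirror solution near 76%. A relative 10% fall gives about 320 only from a control risk near 86%. The article gives none of these risks for any of the three outcomes. No two-sided variant on the frail-elderly rates returns 320.

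**Hospital admission, absolute 10 points, annual rate.** p1 = 0.45, p2 = 0.35, p = 0.40.

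n = [1.960·√0.48 + 0.842·√0.475]² / 0.01 = (1.358 + 0.580)² / 0.01 ≈ 376.

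Power at 320 = Φ[(0.10·√320 − 1.358) / 0.689] = Φ(0.625) ≈ 73%. At 329 it is Φ(0.662) ≈ 75%.

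**18-month risks.** Assuming a constant annual risk: hospital 1 − 0.55^1.5 = 59.2%; nursing home 1 − 0.85^1.5 = 21.6%.

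| Outcome and horizon | Reading of 10% | p1 → p2 | n per group for 80% | Power at 320 |
|---|---|---|---|---|
| Hospital, 12 months | absolute | 45% → 35% | 376 | 73% |
| Hospital, 18 months | absolute | 59.2% → 49.2% | 389 | 72% |
| Hospital, 12 months | relative | 45% → 40.5% | 1,897 | 21% |
| Hospital, 18 months | relative | 59.2% → 53.3% | 1,101 | 33% |
| Nursing home, 12 months | absolute | 15% → 5% | 141 | 99% |
| Nursing home, 18 months | absolute | 21.6% → 11.6% | 217 | 93% |
| Nursing home, 12 months | relative | 15% → 13.5% | 8,525 | 8% |
| Nursing home, 18 months | relative | 21.6% → 19.5% | 5,476 | 10% |

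At 329 per group the 18-month absolute figure for hospital admission is 73%.

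**Detectable with 80% power at 329 per group.**
- Hospital: 10.7 points from 45% (24% relative), or 10.9 points from 59.2% (18% relative).
- Nursing home: 7.0 points from 15% (46% relative), or 8.3 points from 21.6% (38% relative).

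**Mortality.** The article gives no rate, so the claim can be neither confirmed nor refuted. For illustration, an assumed control risk of 20% falling to 10% would have about 94% power at 320.

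**The case against.** The sample-size paragraph does not say that the Costs rates were its inputs. Those rates are medians over studies, quoted in a background section on costs. The trial also excludes terminally ill people and people with dementia symptoms, so its own hospital rate could be lower than 45%. A control risk near 34% makes 320 correct, and 34% lies between the article's two hospital medians, 26% and 45%. This stands. It means the mismatch depends on the 45% rate applying, and the calculation may have been sound on inputs that are not shown.

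A reader might infer that the power statement is wrong for all three outcomes. The documents do not support that. On the absolute reading the sentence is conservative for nursing home placement. For mortality there is nothing to check against, and a missing planning rate is an ordinary omission in a condensed article. The article also describes institutionalization more broadly under Outcomes and measurements (hospital stay, nursing home or home for the elderly) than under Data-analysis (nursing home placement), so 15% may not be the exact control risk for that outcome.

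A reader might also take the relative-reading powers of 8–33% as the trial's real power. The stated number argues against this: 320 follows from an absolute 10 points at a plausible risk, but from a relative 10% only at a risk near 86%. Those figures show what the undefined 10% could lead a reader to believe; they do not estimate what was planned.

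What survives is that the article prints a power for hospital admission and, from the same references, a rate for this population at which that power is not reached on either reading or at either time horizon.

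**Conclusion.** The point holds for hospital admission. If the 45% annual rate applies, power at 320 per group is about 72–73% for an absolute 10-point fall, against the stated 80%. All 658 randomized bring it to 73–75%. The shortfall is thus about 5 to 8 percentage points of power, and the detectable difference is 10.7–10.9 points instead of 10. This is moderate, and it does not show that the trial is too small for its purpose.

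The ambiguous 10% carries the larger risk of misreading. Taken as relative, it would have 21–33% power for hospital admission and 8–10% for nursing home placement.

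The conclusion rests on the two-proportion formula matching the planned chi-square test, on the Costs medians as control risks, and on constant annual risk for the 18-month figures.

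**What to change.** Say that the 10% means absolute percentage points. Replace the single claim with one statement per endpoint for the 658 randomized, each giving its assumed control risk over 18 months, the absolute difference detectable with 80% power, and the equivalent relative reduction. If the Costs rates are the intended inputs, these are about 10.7–10.9 points for hospital admission (18–24% relative) and 7.0–8.3 points for nursing home placement (38–46% relative), where each range spans the annual and 18-month risks. If another control risk was used, such as one near 34%, state it and its source. For mortality, state the assumed risk behind the claim. Add that a non-significant result will not exclude a 10% relative reduction.

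The cost is a rewritten paragraph. No patients are added and the design does not change. The downside is that the stated power for hospital admission becomes slightly less favourable.

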#### Data-analysis

According to the 'intention-to-treat' principle differences between intervention and usual care patients on mortality, hospitalization and nursing home placement (dichotomous outcomes) are tested by both chi-square tests and logistic regression analysis. Differences in time until these events will be analyzed with Cox-proportional hazard modeling. For quality of life (continuous outcome: SF-36, EQ-5D) General Linear Models (GLM), a technique for repeated measures is used to analyze group differences. Possible baseline differences in the outcome measures will be accounted for in GLM. Additional subgroup-analyses will be performed on types of recommendations in the care-plans.

Potential confounding and effect-modification is checked for sociodemographic characteristics, number and type of chronic disease, (I)ADL functioning (GARS), cognitive decline (IQCODE), mood (CES-D), behavioral problems (incontinence, sleep, agitation en aggression), medication use (centralized pharmacy data base) (Table 4) [28-30].

Quality of the data was assured by independent double checks of all forms. Also our institute employs a quality assurance policy. In this respect guidelines on all aspects of research were issued and all projects are subject to audits.

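### The repeated-measures GLM named for SF-36 and EQ-5D would, in its standard form, discard six-month scores of about 18% of randomized persons; a likelihood-based mixed model would keep them

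*Protocol article*

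**What the plan says.** The Data-analysis section of the protocol article fixes the method for the continuous quality-of-life outcomes: "General Linear Models (GLM), a technique for repeated measures is used to analyze group differences". It adds: "Possible baseline differences in the outcome measures will be accounted for in GLM". It does not mention persons with a missing wave, imputation, or a likelihood-based model.

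Table 4 (Outcomes and measurements) schedules SF-36 and EQ-5D at T0, at six months (T1) and at 18 months (T2).

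The Sample size calculation section states: "Anticipating on an annual attrition of 20% (mortality, inability to respond, unwilling) 75 persons per group will be needed". Quality of life is the first listed main outcome and the first basis for the sample size.

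The intention-to-treat statement opens the sentence on the binary outcomes: "According to the 'intention-to-treat' principle differences between intervention and usual care patients on mortality, hospitalization and nursing home placement (dichotomous outcomes". The quality-of-life sentence does not repeat it.

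**The concern.** A classical repeated-measures GLM takes one row per person with every wave filled, so a person without a T2 score also loses the T0 and T1 scores. In a frail population aged 75 and over, two of the three stated causes of loss (death and inability to respond) are tied to health, and so to the outcome itself. The analysed set then leans towards healthier survivors, and valid six-month scores of the others go unused.

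This could matter for the comparison between arms because the trial is also planned to detect lower mortality and institutionalization. If the intervention has those effects, the arms may differ in who remains in the complete set. What is at stake is the validity of the quality-of-life estimate, including the six-month estimate, for which most of the needed data would have been collected.

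**Working it through.** **Inputs from the article.** 658 randomized (Recruitment); equal numbers per arm within practice (Design); waves at 0, 6 and 18 months (Table 4); 20% attrition a year, d = 0.5, two-sided alpha 0.05, 80% power (Sample size calculation).

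**Assumptions added here.** The annual rate is constant; T0 is observed in everyone; nobody who misses T1 returns at T2.

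**The plan's own figure.** n per group = 2 × (1.96 + 0.84)² / 0.5² = 62.8, so 63 by the normal approximation. The two-sample t-test gives 63.8, so 64. The stated 64 reproduces. Whether 75 is the right inflation for attrition is a separate matter and does not enter below.

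**Who is observed.**

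| Group | Formula | Persons | Share of 658 |
|---|---|---|---|
| Seen at T1 | 658 × 0.8^0.5 | 588.5 | 89% |
| Complete to T2 | 658 × 0.8^1.5 | 470.8 | 72% |
| T0 and T1 only | 588.5 − 470.8 | 117.7 | 18% |
| T0 only | 658 − 588.5 | 69.5 | 11% |

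The third row is what a complete-row GLM discards and an all-data model keeps. It is also 20% of those seen at T1 (117.7 / 588.5). If loss is instead linear, 10% at six months and 30% at 18 months, then 658 × 0.9 = 592 are seen at T1, 658 × 0.7 = 461 are complete, and 132 have T0 and T1 only.

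**Power among completers.** Per group, 470.8 / 2 = 235. The smallest effect detectable with 80% power is (1.96 + 0.84) × √(2/235) = 0.26 SD. Power for d = 0.5 is above 99%.

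**Bias.** This was checked by simulation on assumed inputs: a true effect of 0.30 SD at T1 and T2, and correlations of 0.6 (T0–T1), 0.65 (T1–T2) and 0.5 (T0–T2). Loss before T1 was random; a further 20% loss before T2 depended on the T1 score. The slope is the rise in log-odds of loss per SD of worse T1 score.

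| Slope, control / intervention | Complete-case T1 | Complete-case T2 | All-data likelihood T1, T2 |
|---|---|---|---|
| 0 / 0 | 0.30 | 0.30 | 0.30, 0.30 |
| 1 / 1 | 0.30 | 0.30 | 0.30, 0.30 |
| 0 / 1 | 0.41 | 0.36 | 0.30, 0.30 |
| 1 / 0 | 0.19 | 0.24 | 0.30, 0.30 |
| 1 / 0.5 | 0.25 | 0.27 | 0.30, 0.30 |

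Complete-case estimates, adjusted for baseline, go wrong only where the relation between score and loss differs by arm, and they can go either way. The likelihood estimate holds because loss in this simulation depends only on observed scores. The simulation does not cover loss that depends on unobserved scores, or truncation by death.

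**The case against.** The strongest reply is that the article never says incomplete persons are excluded. Listwise deletion is the default of the classical form, and the handling of incomplete records is often left to a full protocol or analysis plan that is not shown here. This stands as a limit on certainty. But the method is named in the article, and its ordinary reading is the complete-row model. Choosing a better method is more than asking for missing detail.

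A reader might infer several stronger points that the documents do not support:

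- **That the method contradicts the intention-to-treat commitment.** That phrase is attached to mortality, hospitalization and nursing home placement. The text leaves open whether it reaches SF-36 and EQ-5D, so there is no contradiction to cite.
- **That the result is unbiased only if loss is completely at random.** This is too strong. Baseline is accounted for in the model, and in the simulation bias was near nil when loss depended on the score alike in both arms.
- **That the fix rescues all 187 persons without a complete record (658 − 471).** About 69 of them have no follow-up score and would contribute nothing to a model of T1 and T2 outcomes either. The gain is about 118 six-month scores, with no T2 score added.
- **That survivor selection by itself shows a material bias.** If survival were 80% versus 90% and the extra survivors scored 0.5 SD lower, the shift would be (0.10 / 0.90) × 0.5 = 0.056 SD. Both inputs are assumed, and a mixed model would not remove this shift.

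The article also offers partial protection. Mortality is a separate outcome, and QALYs weight utility by time spent in a state, so time after death would naturally add nothing. A close relative may complete forms, but that provision appears under direct costs, its reach to SF-36 and EQ-5D is unclear, and it cannot address death.

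**Conclusion.** The point holds as a choice of method that should be improved, not as a fatal flaw. If the GLM is used in its standard form, about 118 of 658 persons (18%; 132 under linear loss) would have an observed six-month outcome discarded. This rests on the plan's own 20% a year, taken as constant, with complete T0 data and no return after a missed wave.

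Power for the planned effect is unaffected. Bias is possible rather than shown: it needs health-related loss that differs between arms. The trial's own hypotheses on mortality and institutionalization make that plausible, but the article gives no figure from which to size it. The simulated range for a true 0.30 SD (0.19 to 0.41 at T1, 0.24 to 0.36 at T2) illustrates what can happen under assumed inputs and is not a forecast for this trial.

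**What to change.** Replace the GLM for SF-36 and EQ-5D by a likelihood-based linear mixed model for repeated measures. T1 and T2 are the outcomes; the terms are arm, visit, arm-by-visit and baseline score; the within-person covariance is unstructured. Include everyone with at least one follow-up score.

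State that intention-to-treat also covers SF-36 and EQ-5D.

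Add one sensitivity analysis that includes deaths, for example an EQ-5D utility of 0 from the date of death. It is needed because quality of life after death does not exist and the mixed model alone does not resolve that.

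The cost is a short change to the Data-analysis section and slightly more analysis work in standard software. No new data are needed, since time to death is already collected (Table 4). The downside is that the mixed model relies on loss being at random given the observed scores, which should be stated as an assumption.

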**Methods:**

*Main study*: The main study concerns a randomized controlled in primary care practices (PCP) with 18 months follow-up and blinded PCPs. Frail persons aged 75 years or older and living at home but neither terminally ill nor demented from 33 PCPs were eligible. Trained community nurses (1) visit patients at home and assess the care needs with the Resident Assessment Instrument-Home Care, a multidimensional computerized geriatric assessment instrument, enabling direct identification of problem areas; (2) determine the care priorities together with the patient; (3) design and execute interventions according to protocols; (4) and visit patients at least five times during a year in order to execute and monitor the care-plan. Controls receive usual care. Outcome measures are Quality of life, and Quality Adjusted Life Years; time to nursing home admission; mortality; hospital admissions; health care utilization.

*Pilot 1*: Three brief postal multidimensional screening measures to identify frail health among elderly persons were tested on percentage complete item response (selected after a literature search): 1) Vulnerable Elders Screen, 2) Strawbridge's frailty screen, and 3) COOP-WONCA charts.

*Pilot 2*: Three nurses visited elderly frail patients as identified by PCPs in a health center of 5400 patients and used an assessment protocol to identify psychosocial and medical problems. The needs and experiences of all participants were gathered by semi-structured interviews.

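### Subgroups by type of care-plan recommendation are formed after randomization and only in the intervention arm, so effect estimates by recommendation type are not randomized comparisons

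*Protocol article*

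**What the plan says.** The Data-analysis section of the Protocol article opens with the randomized comparison: "According to the 'intention-to-treat' principle differences between intervention and usual care patients on mortality, hospitalization and nursing home placement". After the methods for binary, time-to-event and quality-of-life outcomes it adds: "Additional subgroup-analyses will be performed on types of recommendations in the care-plans". It gives no comparator, outcome or model for this analysis and does not label it exploratory or descriptive.

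The Intervention(s) section shows where the recommendations come from. "All frail persons and randomized to the intervention were contacted by one of eight trained nurses"; the first visit includes the RAI-HC assessment, and nurse and patient then rank the problems found. "The nurses design and execute individual suited care-plans that comply with patient priorities". Later visits serve "to evaluate whether the care-needs have changed and adapt the care/plan when needed".

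For the other arm the Abstract (Methods) says only: "Controls receive usual care". Table 4 lists neither the RAI-HC nor care-plan content as a trial measurement in either arm. It does list a health screener for all participants, with "T-1 = pre randomization health screening".

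The next paragraph of the Data-analysis section plans a check of confounding and effect modification for a list of patient characteristics. The list includes chronic disease, GARS, IQCODE, CES-D and incontinence.

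**The concern.** A subgroup analysis in a randomized trial compares the arms within strata that can be identified in both, before treatment can influence membership. Recommendation type meets neither condition. It is fixed after allocation, by the intervention itself, and has no counterpart among controls.

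Patients receive a recommendation because they have a problem and regard it as a priority. Both may predict admission, institutionalization, death and quality of life. A statement about which recommendations help or harm is the kind of result that is readily quoted from such a trial, and it would rest on a comparison that cannot separate the effect of the advice from the reason for giving it.

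**Working it through.** The plan gives no figure for this analysis, so there is none to reproduce. The check has three parts.

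**1. Is the variable defined before randomization and in both arms?**

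| Feature | Intervention arm | Control arm | Source |
|---|---|---|---|
| Nurse contact and RAI-HC | yes, after allocation | none described | Intervention(s); Abstract, Methods |
| Care plan with recommendations | yes, shaped by need and priorities, adapted over time | none described | Intervention(s) |
| Health screener at T-1 | yes | yes | Table 4 |

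Only the last row can define subgroups for a randomized comparison. Because plans are adapted during follow-up, classifying patients by any recommendation ever received would also depend on how long they stayed alive and at home.

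**2. Size of the selection bias for a binary outcome.** Let s be the share of intervention patients with a given recommendation, r1 the risk in recipients and r0 the risk in the other intervention patients. Suppose there is no treatment effect. Randomization then gives the control arm an expected risk of s·r1 + (1 − s)·r0, so:

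- recipients minus all controls = (1 − s)(r1 − r0)
- non-recipients minus all controls = −s(r1 − r0)
- recipients minus non-recipients = r1 − r0

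The documents give neither s nor the risk gap. Assume s = 30% and a gap of 5 to 15 percentage points:

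| Assumed gap | Recipients − controls | Non-recipients − controls | Recipients − non-recipients |
|---|---|---|---|
| 5 points | 0.70 × 5 = +3.5 | −0.30 × 5 = −1.5 | +5 |
| 15 points | 0.70 × 15 = +10.5 | −0.30 × 15 = −4.5 | +15 |

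For example, with r1 = 70% and r0 = 55%, the control risk is 0.30 × 0.70 + 0.70 × 0.55 = 59.5%, and 70 − 59.5 = 10.5 points. If a recommendation goes mainly to fitter patients, the gap is negative and every sign reverses.

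**3. Size for a continuous outcome.** A simulation used 650 patients (the planned total in Sample size calculation), 325 per arm, 4000 runs and no treatment effect. An unmeasured need score drove both the outcome and who received the recommendation (about half of the intervention arm). The need–outcome correlations are assumptions.

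| Assumed correlation | Recipients − controls | Non-recipients − controls | False-positive rate, recipients v controls (nominal 5%) |
|---|---|---|---|
| 0.2 | −0.11 SD | +0.11 SD | 22% |
| 0.3 | −0.17 SD | +0.17 SD | 43% |
| 0.5 | −0.28 SD | +0.28 SD | 84% |

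In the same runs the comparison of the full arms showed 0.00 SD and about 5% rejections.

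**The case against.** **The sentence names no comparator.** This stands. A description within the intervention arm would fit the words and would be harmless. A reader might infer that the article commits to a test against controls. The position of the sentence, directly after the between-group methods, makes that the likely reading but not a certain one. An unseen analysis plan could settle the comparator. It could not turn recommendation type into a randomized subgroup, because controls have no care plan.

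**Confounding could be adjusted for.** In part. T-1 data on mood, function, falls, incontinence and chronic disease exist in both arms and could be used to match or adjust, so the unadjusted figures above may overstate what a careful analysis would show. Adjustment still would not restore randomization: patient priorities and the RAI-HC problem list shape the plan, and neither is recorded for controls.

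**Sound subgroup work is already planned.** This also stands. The effect-modification check covers chronic disease, GARS, CES-D and incontinence. It would be wrong to say that the plan lacks subgroup analysis on patient characteristics.

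**Stronger readings to avoid.** A reader might infer that care aimed at the sickest will appear harmful whatever it truly does. It need not: the observed contrast is the true effect plus the selection bias, so a benefit larger than the bias would still show as a benefit. A reader might also set the 10.5 points beside the 10% reduction in Sample size calculation and conclude that the bias equals the effect the trial is sized for. The article does not say whether that 10% is absolute or relative, and 10.5 is only the upper end of an assumed range.

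**Conclusion.** The concern holds in a limited form. Recommendation type is a post-randomization variable that exists only in the intervention arm. Any effect estimate based on it is therefore a non-randomized comparison, open to confounding by need and patient priorities. This follows from the article's own account of the intervention and needs no numerical assumption.

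The size and direction of the bias are unknown. The range of 3.5 to 10.5 points rests on the assumed share and gap and on no adjustment; the simulated error rates rest on the assumed correlations. The analysis is additional: no sample size, main outcome comparison or economic result depends on it. The point therefore merits correction but does not threaten the trial's main conclusions.

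**What to change.** Reword the sentence so that recommendation types are reported only as a description of what the intervention arm received, labelled non-randomized, with no effect estimates attached.

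Base subgroup claims on treatment-by-subgroup interaction tests that use T-1 values from both arms. Build on the effect-modification check already listed (GARS, CES-D, chronic disease, incontinence) and add mobility/falls, which the screener also records. State that T-1 values are used, since Table 4 shows that these measures are repeated during follow-up.

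The cost is an edit of a sentence or two in the analysis section. All the T-1 measures are already collected, so no new data are needed.
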